# Chitosan nerve tube for primary repair of traumatic sensory nerve lesions of the hand without a gap: study protocol for a randomized controlled trial

**DOI:** 10.1186/s13063-015-1148-5

**Published:** 2016-01-26

**Keywords:** Nerve lesions of the hand, peripheral nerve surgery, nerve tube, sensory outcome

## Abstract

**Background:**

Complex peripheral nerve injuries of the hand include at least 300,000 cases per year in Europe. The standard treatment involves a microsurgical end-to-end suture of traumatic sensory nerve lesions of the hand without a gap. The objective of this study protocol is to evaluate whether the additional use of a chitosan nerve tube in primary repair of traumatic sensory nerve lesions of the hand without a gap has an effect on the recovery of sensitivity.

**Methods/Design:**

We planned a randomized double-blind controlled multicenter trial with a parallel group design in order to show superiority for the additional use of a chitosan nerve tube. This study will enroll 100 participants with traumatic sensory nerve lesions of the hand without a gap from three Trauma Care Centers. Participants will be randomized in a 1:1 ratio to primary microsurgical repair of the injured nerve with the additional use of a chitosan nerve tube or direct tension free microsurgical repair of the injured nerve alone. The static two-point discrimination of the injured finger after 6 months will be the primary outcome parameter.

**Discussion:**

In the proposed study, the additional use of a chitosan nerve tube for a primary microsurgical repair of traumatic sensory nerve lesions of the hand without a gap will be evaluated in a prospective randomized double-blind controlled multicenter trial for the first time to create the highest possible evidence for the procedure.

**Trial registration:**

ClinicalTrials.gov Identifier: NCT02372669.

Protocol Registration Receipt on 27 February 2015.

## Background

Complex peripheral nerve injuries of the hand include at least 300,000 cases per year in Europe [1]. In recent decades, considerable efforts have been made to support peripheral nerve regeneration but often with limited and minor success. At least one-third of patients will never regain normal sensitivity of the injured finger [2]. Subsequently, nerve dysfunction may lead to impaired function of the whole hand. This is especially true if the thumb as well as the index and small fingers are affected. Painful neuroma formation is frequently observed after peripheral nerve injuries of the hand. Sixty percent of these patients are observed with persistent pain lasting for years in up to 10 % [3–5].

Injured nerves do not spontaneously restore their function. Continuity of the nerve has to be re-established by microsurgical intervention. Standard treatment for traumatic sensory nerve lesions of the hand without a gap is an end-to-end suture, whereas nerve gaps are generally treated using autologous nerve grafts [6]. However, functional results often are disappointing, and painful neuroma formation is frequently observed after nerve repair. Moreover, autologous nerve grafting comes along with significant donor site morbidity [7]. To overcome this problem, alternative treatment options such as biosynthetic nerve grafts (little bio-absorbable implantable tubes) have been developed, primarily for the repair of short gap injuries. Nerve tubes should bridge the gap in this situation, protect the nerve from scar formation, and guide the regenerating axons to the distal stump [7]. The basic design of these nerve tubes is similar, but they are made of different absorbable biomaterials. For chitosan, a bioactive effect is reported [8–11].

This study should focus on the use of nerve tubes in addition to the primary microsurgical repair of traumatic sensory nerve lesions of the hand without a gap. So far, evidence for this approach is lacking. However, consolidated findings regarding tension in nerve repair and reconstruction of nerve gaps using chitosan tubes, as well as the biomaterial chitosan itself, are available to support the procedure.

Above all, tension in the repaired nerve prohibits the healing process [12]. The use of a nerve tube allows a tension-free suture. Possibly, that is the reason why nerve repair using a nerve tube bridging a gap of several millimeters was shown to have even better results than primary repair in injuries without nerve loss [13].

Promising clinical results have already been observed for nerve gap reconstruction using nerve tubes. The meta-analysis of Meek et al. summarizes the available literature and reports good and excellent results after 11 months in 75 % of the cases [14]. However, the authors still conclude that prospective randomized controlled trials with a systematic comparison of standard treatment and biosynthetic implants are lacking and that a systematic evaluation of only one biomaterial is required. Whether the repair of nerve lesions without a gap using a chitosan nerve tube can obtain comparable results is uncertain.

Chitosan, a derivative of chitin, is a biocompatible and biodegradable material and is similar to natural glycosaminoglycans. In vivo studies showed positive effects on the survival and orientation of the Schwann cells [8], as well as on the survival and differentiation of the neuronal cells [9, 10]. Furthermore, the substance itself seems to prevent painful neuroma [11]. Therefore, it potentially is the ideal material for nerve tube reconstruction. In this study, chitosan nerve tubes will be tested for use in treating traumatic sensory nerve lesions of the hand without a gap for the first time.

The assessment of sensory recovery after peripheral nerve surgery also remains challenging. Sensitivity of the hand is a complex process and can only be assessed with several tests addressing a variety of partial functions. Strictly speaking, the two-point discrimination (2-PD) is just an assessment tool for tactile gnosis. Tactile gnosis is the ability to recognize shapes and is a marker of functional recovery [15]. An age-related decline was shown in healthy individuals [16]. Based on that fact, nerve regeneration has often been postulated also to decrease with age [17], but this has not yet been proven. More importantly, interfering variables such as the distance from the lesion to the finger pulp exist. This distance was the only interfering variable that was shown in Meeks meta-analysis [14]. However, measuring the two-point discrimination provides a ratio of scaled values, making it particularly suitable for a scientific approach. The Semmes-Weinstein monofilament test, in contrast, assesses the ability for the perception of cutaneous pressure and is a marker for re-innervation in a stricter sense but does result in categories and thereby in a minor level of measurement [18].

The objective of this study protocol is to evaluate whether the additional use of a chitosan nerve tube in the primary microsurgical repair of traumatic sensory nerve lesions of the hand without a gap has an effect on convalescence and functional results.

### Hypotheses

#### Alternative hypothesis (H1)

The additional use of a chitosan nerve tube in the primary microsurgical repair of traumatic sensory nerve lesions of the hand without a gap will be superior compared with microsurgical repair alone.

#### Null hypothesis (H0)

The additional use of a Chitosan nerve tube in the primary microsurgical repair of traumatic sensory nerve lesions of the hand without a gap will be equal to or inferior to microsurgical repair alone.

## Methods/Design

### Design of the study and setting

To answer the question of whether the additional use of a chitosan nerve tube in primary microsurgical repair of traumatic sensory nerve lesions of the hand without a gap will improve the recovery of sensitivity, a randomized controlled multicenter trial with parallel group design was planned to show superiority for the additional use of a nerve tube. This study will enroll participants with traumatic sensory nerve lesions from three Centers: the BG Trauma Center Ludwigshafen (Ludwigshafen, Germany), BG Trauma Center Frankfurt am Main (Frankfurt am Main, Germany), and BG Bergmannsheil Bochum (Bochum, Germany). Trauma Center Ludwigshafen will be the executive study center.

### Screening

After being informed about the study and its potential risks, all individuals with traumatic sensory nerve lesions of the hand without a gap will be consecutively screened for eligibility until the recruitment period is over. Informed consent comprises a description of the procedures and objectives of the study and the follow-up period. Patients are informed that participation is completely voluntary and does not come with direct benefits and that denial does not come with disadvantages for the participant. The use by the trial of an already accredited and CE-certified product will be explained but in a blinded study setting. Potential adverse events regarding surgery in general and regarding the implant in particular are explained. The participants have to give their assent for blinded therapy and for the follow-ups. Participants are instructed to report any exceptional events immediately to the study center. Screening will be performed by younger physicians in the emergency ward who are not involved in randomization, surgery, or follow-up. A case report form will be prepared that will be used for the whole investigation.

### Recruitment

A two-phase recruitment will be conducted with a preoperative and intraoperative survey. After an individual has been found to be eligible by checking the preoperative inclusion and exclusion criteria, immediate operative treatment will follow. In the second phase of recruitment, the surgeon will explore the wounds and check the intraoperative inclusion and exclusion criteria. The surgeons are experienced physicians and are not involved in the screening or follow-up.

### Randomization

Finally, the enrolled participants will be randomized in a 1:1 ratio by alternating lists in the operating room to primary microsurgical repair with the additional use of a chitosan nerve tube or direct tension-free microsurgical repair of the nerve alone. Final enrollment and randomization following a fixed scheme will be performed by experienced surgeons who are not involved in the screening or follow-up. The CRFs will be accomplished for follow-up.

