### Blinding

The kind of intervention is blinded for the participant and for the follow-up investigator, who was not involved in the surgery. In all study centers, medical postgraduates were employed for the follow-up examination. These raters are explicitly excluded from the screening, randomization, and operative procedure. The randomization list is kept locked in the operating room and is only available to the trial leaders and the surgeons for the process of randomization. After enrollment, only a running number on the CRFs will identify the participant’s position in the list. The rater only has access to the CRFs and not to the randomization list. Adherence to chronological randomization by the list will be monitored by an executive study center. The operation record will only include information about participation in the trial but will not include information about dedicated group. Unblinding is only permitted after dropout or after completion of the trial and can only be performed by the trial leaders.

Figure 1 shows the study flowchart.

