### Participants

All individuals with a fresh traumatic wound of the hand and with the clinical suspicion of traumatic sensory nerve lesions of the hand without a gap will be consecutively screened for eligibility during the preoperative and intraoperative periods.

Preoperative inclusion criteria are as follows:Clinical suspicion of traumatic sensory nerve lesions of the hand without a gap (lesion from the distal area of the carpal tunnel to the end finger joint with complete loss of a nerve-specific receptive field of the finger).Age between 18 and 67 years.Trauma occurred in the previous 72 h.Signed informed consent.

Preoperative exclusion criteria are as follows:Amputated or avascular fingers.Infection of the wound.Known pre-existing impaired sensibility of the injured finger or the opposite side.Allergy to chitosan.Pregnancy.Known immunodeficiency.Participation in other trials.

Intraoperative inclusion criteria are as follows:Verification of a traumatic sensory nerve lesion of the hand without a gap.Nerve can be sutured in end-to-end fashion.

Intraoperative exclusion criteria are as follows:Avascular fingers.Multiple nerve lesions, which cannot be randomized uniformly.Nerve injuries with a gap.

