## Discussion

Standard therapy for traumatic sensory nerve lesions of the hand includes a direct tension-free microsurgical repair for lesions without a gap and autologous nerve grafting from another body region for lesions with a gap [6]. Alternatively, nerve gaps are increasingly reconstructed using nerve tubes to prevent donor site morbidity. A recent meta-analysis shows good and excellent clinical results for this approach [14]. However, prospective controlled single trials are still lacking, and hardly any systematic comparison of standard treatment and the use of nerve tubes are available [14]. The proposed study will compare standard treatment and the use of nerve tubes in a prospective controlled trial setting. Some hand surgery departments also use nerve tubes in addition to a direct nerve suture for lesions without a gap in hopes of improving the results, but such an effect has not yet been proven. Therefore, the major study objective of this trial will be to answer the question of whether the additional use of a chitosan nerve tube in primary microsurgical repair of traumatic sensory nerve lesions of the hand without a gap will improve the recovery of sensitivity. The results will have a direct implication on this common, but as of yet scientifically unproven, practice. A potential study limitation is an example of risk of selection bias because of the quasi-randomization method of using alternating lists. This limitation is due to the emergency surgery setting of the study. Of course, the determined power of 80 % power does also come along with a risk for type II errors of 20 %, but that is conventional for most medical trials. In addition, there is experimental evidence that the use of a chitosan nerve tube may improve functional outcome and reduce the incidence of a painful neuroma [7–11, 24, 25]. The proposed study will test the chitosan-based implant in a clinical setting. If we obtain promising results, we will expand the use of the chitosan nerve tube to use in further studies for traumatic sensory nerve lesions of the hand with a gap as an alternative to autologous nerve grafting and for traumatic nerve lesions of the forearm that include motor axons and therefore have an even more significant burden of disease.

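### Allocation by alternating lists lets the surgeon who makes the final eligibility decision know or deduce the next arm, so the trial is open to selection bias and is quasi-randomized, not randomized as labelled

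*Protocol article*

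**What the plan says.** The Randomization section states that participants "will be randomized in a 1:1 ratio by alternating lists in the operating room", and adds: "Final enrollment and randomization following a fixed scheme will be performed by experienced surgeons". Under Recruitment, in the second phase "the surgeon will explore the wounds and check the intraoperative inclusion and exclusion criteria". Two of the intraoperative criteria under Participants show how far this rests on judgement: "Nerve can be sutured in end-to-end fashion" for inclusion and "Multiple nerve lesions, which cannot be randomized uniformly" for exclusion.

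The Blinding section says that the list is locked in the operating room and "is only available to the trial leaders and the surgeons for the process of randomization". It describes one check on the sequence: "Adherence to chronological randomization by the list will be monitored by an executive study center". It also says that the running number on the case report form (CRF) shows the participant's place in the list.

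The Discussion acknowledges a "risk of selection bias because of the quasi-randomization method of using alternating lists" and attributes it to the emergency setting. The title, the abstract's methods paragraph and the design section call the trial randomized without that qualification. The abstract's discussion paragraph says that the trial will yield evidence of the highest attainable grade.

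**The concern.** Random allocation protects a comparison only if the person deciding on entry cannot foresee the assignment. Here one person explores the wound, sees the state of the nerve ends, applies criteria that leave room for judgement, and then allocates from a sequence that can be worked out. A surgeon who expects a poor result could, without any intent to mislead, find a borderline lesion unsuitable when one arm is next and suitable when the other is.

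The groups would then differ before treatment in ways that nobody recorded. A difference in two-point discrimination at 6 months could not be attributed cleanly to the tube.

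The running number adds a smaller problem. If the list strictly alternates, odd and even positions correspond to arms. A rater who learned one participant's arm could infer the rest of that list.

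**Working it through.** **1. The plan's own figure.** The Sample size section gives a control mean of 8 mm, SD 3 mm, difference 2 mm, two-sided t-test at 0.05 and power 80%. The normal approximation is n = 2(1.96 + 0.8416)² × 3² / 2² = 35.3, so 36 per group. The exact t-test gives 36.31, rounded up to 37, with power 80.8%. The stated 37 is reproduced. The 50 randomized per group imply an allowance of 1 − 37/50 = 26% for loss. The sample size is not in dispute.

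**2. How predictable is the next arm?** Planned recruitment is 50, 25 and 25 by centre. I read alternating as strict A-B-A-B; the article does not print the list. Under that reading, each allocation after the first on a list follows from the one before.

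| Scheme | Correctly foreseen, of 100 |
|---|---|
| Alternation, one list per centre (49 + 24 + 24) | 97 |
| Alternation, one list overall | 99 |
| Alternation, list read ahead | 100 |
| Concealed, fixed blocks of 4 | about 70 |
| Concealed, blocks varying over 4, 6, 8 | about 67 |
| Concealed, simple randomization | about 50 |

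The last three rows are simulated for someone who knows all earlier allocations at the centre and makes the best guess. The fair comparator for the remedy below is 67, not 50.

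**3. What could that do to the result?** The documents give neither a diversion rate nor a direction, so these are assumptions. Suppose there is no true effect, and the surgeon turns away the worst fraction q of candidates whenever the tube is next. Let ρ be the correlation between the prognosis visible at surgery and the 6-month outcome. The tube-arm mean then shifts in its favour by

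bias = ρ × SD × φ(z) / (1 − q), with z the upper-q normal quantile.

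For q = 0.10, z = 1.2816 and φ(z) = 0.1755, so φ(z)/(1 − q) = 0.195. The standard error at 37 per group is 3 × √(2/37) = 0.697 mm. Bias divided by this is the noncentrality of a t-test with 72 degrees of freedom. The slight loss of variance in the selected arm is ignored.

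| ρ | Bias, q = 10% | Noncentrality | Type I error, q = 10% | q = 5% | q = 20% |
|---|---|---|---|---|---|
| 0.3 | 0.18 mm | 0.25 | 5.7% | 5.2% | 7.3% |
| 0.5 | 0.29 mm | 0.42 | 7.0% | 5.6% | 11.5% |
| 1 (perfect foresight) | 0.59 mm | 0.84 | 13% | 7.5% | 32% |

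The bottom row is a ceiling for each q under this one-way pattern. If surgeons also turned away the best candidates when the control arm was next, the shift would double.

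**4. What the safeguards reach.**
- Monitoring of list order sees patients who were entered, not one declared ineligible at exploration.
- The count of dropouts before randomization, promised at the end of the outcomes section, may leave a trace of such patients. As described, it does not tie them to the arm that was next.
- Blinding of participant and rater addresses measurement, not entry.
- The analysis of covariance adjusts for centre and lesion-to-pulp distance. Selection on those two would be handled, but selection on the condition of the nerve ends or other prognosis seen at surgery would not.

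**The case against.** The strongest reply is that the authors knew this and said so. The Discussion names both the method and its risk, and gives a reason. Several protections are also real. Screening is consecutive and done by physicians uninvolved in allocation or surgery. Consent precedes the operation. The list is locked and, as the Randomization section is ordered, consulted once a participant is enrolled. Operation records omit the arm. The covariate chosen is the one that the Background reports as the only interfering variable in the cited meta-analysis.

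Much of this stands, and it rules out some stronger readings:
- A reader might infer that the list lies open and every next allocation is known. The text supports only known or deducible. The count of 97 to 99 requires awareness of the previous case on that list. The article does not say how surgeons learn of earlier cases or whether each centre has its own list.
- A reader might infer that the true error rate is 13% or more. That requires surgeons to foresee each 6-month result perfectly.
- A reader might infer that no analysis helps at all. Adjustment for centre and distance deals with part of it.

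The reply does not remove the weakness. Disclosure does not conceal the sequence, and it leaves the Discussion at odds with the unqualified label elsewhere. The emergency setting explains little: the surgeon already stops in theatre, checks criteria and consults a locked list, and opening a numbered envelope is the same step.

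**Conclusion.** The point holds as a weakness in allocation concealment, together with an inconsistent label. The surgeon who decides entry can know or deduce the next arm in nearly all cases if earlier cases are known, and the safeguards described cover this only in part. What remains is selection on intraoperative prognosis that is not measured.

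The size is unknown. With 10% one-way diversion, SD 3 mm, 37 per group and no true effect, a moderate correlation (0.3 to 0.5) gives a bias of about 0.2 to 0.3 mm and a type I error of 5.7 to 7%. Perfect foresight gives the upper bound of 0.59 mm and about 13%. Diversion rate, direction and correlation are all assumed.

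Nothing in the documents shows that diversion has occurred. The objection is that it could, and that the planned records would not let a reader exclude it. That is enough to make the unqualified term randomized, and the claim to the highest grade of evidence, unsupported for patients allocated by alternation.

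**What to change.** By amendment, for all remaining participants:
- Replace the alternating lists with a computer-generated sequence in randomly varying blocks, stratified by centre.
- Hold it in sequentially numbered, opaque, sealed envelopes in the same locked place, or behind a phone or web service. Reveal the assignment only after the intraoperative eligibility form is signed.
- Use CRF numbers that do not encode the position in the list.

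For the trial as a whole:
- Record the date of the switch and report results by allocation method.
- List every intraoperative exclusion in order, against the allocation that was next.
- Describe the part enrolled under alternation as quasi-randomized throughout, including the title and abstract of the final report.

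The cost is a short amendment and a set of envelopes per centre, with no extra staff or patients; 37 evaluable and 50 randomized per group still apply. There are two limits. Participants already enrolled stay quasi-randomized. Recruitment was planned for 12 months and was under way at publication, so few may remain and the analysis by allocation method may have little power. The exclusion listing and the labelling are worthwhile at any stage.

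Varying blocks still allow some guessing (about 67 of 100 when past allocations are known), which is why the reveal must follow the signed form.
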